### Endline survey

Similar strategy from the baseline survey will be followed during the endline survey.

### Cohort tracking

Cohort tracking for end line is essential and therefore participant workers are contacted every 2 months to update essential contact and personal information and details about work, including if she has a new job. Any dropout is also explored to understand the reason. Moreover, attempts will be made to conduct endline interviews with the worker even if she leaves the factory and changes residence within the same area. If she is traced and refuses to be interviewed the reason will be recorded. If she cannot be found in her previous address, we will try to track her through additional contact information. It is assumed that management staff will not move jobs and can be easily contacted through the factory management only the workers are being tracked by icddr,b. Contact information of the study participants is stored separately from the survey data and kept under lock and key.

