All the study participants were given a unique code and all the indentifying information are kept in a separate file exclusively accessed by the research team and used for tracking the individuals over the intervention period and to contact them during the endline survey. Care will be taken to present the research findings in sufficiently aggregated form to ensure that no participating factories and workers can be identified.

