The primary and secondary outcomes are based on self-reporting and we cannot know if there is under-reporting. This is always a risk in questionnaire-based outcomes and especially where participants may feel the need to protect their family by under-reporting partner violence or may fear reprisals for accurate reporting of workplace violence. We have taken very considerable care around confidentiality, including interviewing women outside work, and hope this will minimise these under-reporting risks.

We have accommodated some loss to follow up in the sample size calculation, but job mobility is a feature of the industry and we are concerned that more women and managers may leave the factories than anticipated. Also any staff leaving intervention factories during the intervention would not get the full dose. Intention to treat requires cohort follow up but mobility may dilute apparent impact. Further absolute loss to follow up will reduce the study’s power to detect the anticipated difference between arms.

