As for the workers, the managers in the intervention factories were younger than in the control factories. About 45% of the management staff in the control factories were 35 years or older, compared to 30% of management staff in the intervention factories. Education did not differ significantly between arms. About half of the management staff from both the groups (intervention 49%; control 54%) had 6-10 years of education. Most of the management staff in the intervention factories (49%) had been working there for less than 2 years compared to 13% of those in the control factories. Management staff from the control factories had a greater average monthly income (BDT 24,751 or USD 321) compared to the intervention factories (BDT 21,147 or USD 275).

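### The plan assumes managers will not change jobs and describes no route to those who leave, though its own text expects departures, and baseline tenure suggests that loss may differ by arm

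*Protocol article*

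**What the plan says.** **Cohort tracking.** On workers: "participant workers are contacted every 2 months to update essential contact and personal information". A worker who leaves the factory is still sought for the endline interview. On managers: "It is assumed that management staff will not move jobs and can be easily contacted through the factory management", and "only the workers are being tracked by icddr,b".

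**Data collection methods and Endline survey.** Managers were interviewed at the factory during office hours. The endline is to follow a similar strategy.

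**Sample size.** The management survey needs 183 per group, raised to 200 for an anticipated 10% loss.

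**Limitations.** "job mobility is a feature of the industry and we are concerned that more women and managers may leave the factories than anticipated". The same paragraph adds that staff who leave intervention factories while the programme is running miss part of it, and that "Intention to treat requires cohort follow up but mobility may dilute apparent impact".

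**Table 3.** Managers with 0-2 years in the factory: 49.2% intervention, 13.0% control. With six or more years: 22.6% and 64.5%. The accompanying text draws attention to the same contrast.

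**Ethics and dissemination.** Identifying information on all participants is held in a separate file, "used for tracking the individuals over the intervention period and to contact them during the endline survey".

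**The concern.** The assumption about managers is an operating rule: it decides who is followed up. The article's own text contradicts it in two places, the Limitations and the 10% loss allowance. If the rule is applied as written, contact and interview both depend on the manager still being at the factory, so the endline manager sample could consist largely of those who stayed.

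Two features make this more than a wording problem. First, recent joiners are far more common in the intervention arm. If they leave more often than long-serving managers, loss will be higher in that arm. Second, the loss may be informative. Managers who leave an intervention factory during the programme (November 2016 to August 2017) are the ones with incomplete exposure, and a comparison of stayers would drop them from the intervention arm only. Adjustment for baseline characteristics cannot supply outcomes that were never collected.

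The outcomes at stake are the four that managers report: gender attitudes, knowledge of laws and policies, attitudes to laws and policies, and burnout.

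**Working it through.** **1. The plan's own figure.** Inputs from Sample size: 50% baseline, 30% effect read as relative (50% v 65%), two-sided 5%, 80% power. The two-proportion formula gives 170 per group without continuity correction and 183 with it, so the stated 183 is reproduced as the continuity-corrected figure. The 10% allowance leaves 195 × 0.90 = 175.5 (about 176) intervention managers and 200 × 0.90 = 180 control managers. Uncorrected power at those numbers, ignoring clustering, is 81.9%.

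**2. The passages side by side.**

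| Section | Managers leaving | Way to reach them |
|---|---|---|
| Cohort tracking | assumed not to happen | through factory management; no active tracking |
| Sample size | 10% loss allowed | – |
| Limitations | may exceed what was anticipated | – |
| Data collection methods, Endline survey | – | interview inside the factory |
| Ethics and dissemination | – | identifying details held for all participants, for endline contact |

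The first row does not fit the second or third. A contact file exists, but no procedure applies it to managers who have left.

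**3. How tenure carries into loss.** Short tenure covers 0.492 × 195 ≈ 96 intervention managers and 0.130 × 200 = 26 control managers. If loss over 24 months is *a* for 0-2 years' tenure and *b* for longer tenure:

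- intervention loss = 0.492*a* + 0.508*b*
- control loss = 0.130*a* + 0.870*b*
- gap between arms = 0.362(*a* − *b*)

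**4. Illustration with assumed yearly exit rates.** The article gives none. Yearly exit *s* over two years gives loss 1 − (1 − *s*)², taking every leaver as lost. For *s* = 5%, 15% and 25% this is 9.75%, 27.75% and 43.75%.

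| Yearly exit, 0-2 years / longer | Loss, intervention | Loss, control | Managers left | Power, uncorrected |
|---|---|---|---|---|
| 5% / 5% | 9.75% | 9.75% | 176 / 180 | 82% |
| 15% / 5% | 18.6% | 12.1% | 159 / 176 | 79% |
| 25% / 5% | 26.5% | 14.2% | 143 / 172 | 77% |

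For example, 15% / 5%: 0.492 × 0.2775 + 0.508 × 0.0975 = 0.186, and 0.130 × 0.2775 + 0.870 × 0.0975 = 0.121. Power is for 50% v 65%, ignoring clustering. If half of the leavers were reached, this row would become 9.3% v 6.0%, leaving 177 and 188.

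**5. Possible bias.** If leavers differ from stayers by *d* on the outcome, equally in both arms, a comparison of stayers is biased by (loss gap) × *d*. With *d* assumed at 10 to 30 points, the 15% / 5% row (gap 6.5 points) gives 0.7 to 2.0 points, and the 25% / 5% row (gap 12.3 points) gives 1.2 to 3.7 points. The planned effect is 15 points (50% v 65%).

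**The case against.** The strongest reply is that uneven loss is a forecast. A reader might infer from Table 3 that the manager cohort will certainly lose more people in the intervention arm. The article does not support that. It reports no manager turnover in either arm, and short tenure may reflect newer or expanding factories, or which managers each factory put on its own list. With equal exit rates the gap is zero and the loss falls within the planned 10%. This objection stands, so the point is worded as a possibility.

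A reader might also set 176 retained managers against the required 183 and call it a shortfall. That overstates the cost: 183 includes a continuity correction, and uncorrected power at 176 and 180 is still about 82%.

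Nor does the article show that leavers are unreachable. Factories may know where they went, and contact details are held. What is shown is only that no procedure for reaching them is described.

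Finally, the Limitations already disclose possible manager turnover and loss of power, and the analysis section plans to compare baseline and endline samples and control for differences. That helps with measured imbalance such as tenure. It does not help with unmeasured differences between leavers and stayers, and disclosing the risk leaves the tracking rule unchanged.

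**Conclusion.** The concern holds in limited form. The tracking rule for managers rests on an assumption that the Limitations contradict and that fits poorly with the 10% loss allowance, and following it leaves no described route to managers who leave. The article itself says that intention to treat needs cohort follow-up, and its analysis section applies the same approach to secondary outcomes.

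The size is uncertain. Under the assumed exit rates the gap in loss between arms runs from 0 to about 12 points, with power from about 82% down to 77%. All of this assumes that no leaver is reached and ignores clustering. The more serious risk is selective loss, of the order of 1 to 4 points of bias in the two unequal scenarios if leavers differ from stayers by 10 to 30 points.

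The IPV and workplace-violence primary outcomes are untouched, as is management style, because workers report all of them. The change should be made, but it does not threaten the main conclusions of the trial.

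**What to change.** - In Cohort tracking, delete the assumption that managers stay, so that the section agrees with the Limitations and the 10% allowance.
- Use the contact information already held to phone managers before endline and record who has left.
- Attempt endline interviews outside the factory with those who have left, as is done for workers.
- State that managers who leave remain in the intention-to-treat set for the manager outcomes.
- Report manager loss by arm and by baseline tenure.

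Cost: calls to up to 395 managers and some off-site interviews by the existing survey team. Managers were interviewed only inside factories at baseline, by a separate team from the workers' interviewers, so some interviewer time outside the factory has to be planned. No new participants are needed and the design does not change. The endline (September to November 2018) was still ahead when the article was written, so the change could be made in time.

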### Statistical methods: Data analysis

Intention-to-treat (ITT) analysis will be used for assessing the impact of HERrespect. Thus, all the workers selected for the study will be included in the analysis. The primary analysis will involve comparison between intervention and control factories for assessing the impact of full HERrespect intervention (group sessions and factory-wide mobilization) over control. First the data from intervention and control factories and baseline and endline samples will be compared and Chi-square (for categorical variables) and t-tests (for continuous variables) will be performed to test whether there are differences in prevalence of background characteristics. If differences between intervention and control factories and baseline and endline samples are evident, the pre-existing differences will be controlled in subsequent analyses. The impact of HERrespect intervention on main outcomes of interest will be assessed using risk ratios derived from binary regression analyses adjusting for baseline rates. All analyses will be adjusted for the potential factors associated with the outcomes of interest. The same approach will be followed for assessing the secondary outcomes.

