### Trial design

The trial employs a quasi-experimental design. It is being conducted in four intervention and four control factories. In the intervention factories a randomly selected cohort of married female line workers, a cohort of male line workers, and all middle management staff received the main intervention. In addition, factory-wide campaigns were carried out, and a community activity in one intervention community. For the evaluation, two cohorts have been established and will be followed up over 24 months in each of the intervention and control factories. One is a cohort of randomly selected female line workers (100 per factory) and the second is a cohort of selected management staff with frequent interaction with workers (50 in each factory). Two different questionnaires are administered for workers and management staff (see Additional files 1 and 2). All the workers and management staff from these cohorts were interviewed at baseline, and will be interviewed in the endline. The baseline was conducted before the intervention started, while the endline will be conducted 24 months post-baseline.

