### Limitations

There are constraints on research in the ready-made garment industry in Bangladesh which had to be accommodated in the study design. Factories had strict preference for being included in the study as an intervention or control factory, which the study had to adhere to. This precluded use of a randomisation into the study arms. This means that confounders could not be allocated between arms using randomisation and so have to be measured and adjusted for in analysis where possible. We cannot be sure that all confounders will be measured and adjusted for, but focus on the main possible ones. This will slightly weaken our confidence in the results but having some comparison arm is a strength even if allocation to arm was not random.

We had to take into account the real circumstances of location on the ground and were also not able to match intervention and control factories by location. We have no reason to believe this will affect the results.

In one factory, the number of eligible workers was less than 100. Therefore we recruited all possible eligible workers (77) and relaxed the criteria of duration of employment from 12 to 10 months (23). This is unlikely to impact the results.

The sample (50) for the management survey was selected by participating factories except in one, where the number of management staff was lower than the requirement, so all management were recruited. We recognize that biases may have been introduced in the management sample due to purposive selection conducted by the factories. Any factory approached with such an intervention is likely to use the same strategy of worker and management staff selection. As the intention is to assess impact of an intervention that is feasible to implement and can be scaled up in future, the current sample selection strategy would show the real impact of such intervention.

It is possible that we will find it hard to deliver the full dose of the intervention in factories if managers are reluctant to release workers and managers for periods of 2-3 h for sessions and some simple amendments to sessions may be needed to accommodate available time. This may impact intervention fidelity and ultimately impact.

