### Background characteristics of the study sample

Table 3 shows the participants’ background characteristics by study arm. Workers in the intervention factories were generally younger than those in the control factories. In terms of age, 71% of workers from the intervention factories and 58% from the control factories were between 20 and 29 years. In terms of education, workers in the intervention factories were more educated than the control factory workers. In the intervention factories 48% had 6-10 years of education compared to 34% in the control factories. About 24% of the workers from the control factories had no education compared to 14% of those from the intervention factories. In the intervention factories, 54% of workers had been working there for less than 2 years, compared to 20% of those in the control factories. There was no difference in average monthly earnings between arms.

**Table 3 Tab3:** Comparison between intervention and control groups by background characteristics

Characteristics	Worker survey			Management survey		
	Intervention % (n)	Control % (n)	*P*-value	Intervention % (n)	Control % (n)	*P*-value
N	400	400		195	200	
Age in years						
15-19	8.3	1.3		1.0	0.0	
20-24	36.5	24.8		13.3	2.5	
25-29	34.3	32.8	0.000^a^	25.6	23.5	0.000^a^
30-34	16.3	24.0		30.3	29.5	
≥ 35	4.8	17.8		29.7	44.5	
Level of education						
No education	14.3	23.6		0.0	0.0	
1-5 years	32.0	40.3		3.6	7.0	
6-10 years	48.3	34.3	0.000^a^	48.7	53.8	0.118
11-12 years	4.8	1.8		30.8	21.1	
13-15 years	0.8	0.0		9.7	12.6	
> 15 years	0.8	0.0		7.2	5.5	
Duration of work in the current factory						
0-2 years	53.5	20.0		49.2	13.0	
3-5 years	31.8	43.5	0.000^a^	28.2	22.5	0.000^a^
6 or more	14.8	36.5		22.6	64.5	
Mean earnings per month	8454.6	8555.9	0.290	21,146.5	24,751.1	0.017^b^

^a^Significant at 1% level of significance

^b^Significant at 5% level of significance

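### Control of background differences is partly conditional on significance tests that name no allowance for factories, and the between-wave version of those tests is a weak screen for selective loss

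*Protocol article*

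**What the plan says.** Under Statistical methods: Data analysis, the protocol article compares intervention with control factories, and baseline with endline samples: "Chi-square (for categorical variables) and t-tests (for continuous variables) will be performed to test whether there are differences in prevalence of background characteristics". The consequence follows: "If differences between intervention and control factories and baseline and endline samples are evident, the pre-existing differences will be controlled in subsequent analyses". No threshold for an evident difference is given for this step, and no cluster-adjusted or paired version of the tests is named.

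The section also contains adjustment that carries no test condition. Effects are to be "risk ratios derived from binary regression analyses adjusting for baseline rates", and "All analyses will be adjusted for the potential factors associated with the outcomes of interest". No variables are listed.

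Under Limitations, the article explains that factories' preferences ruled out randomisation, so that "confounders could not be allocated between arms using randomisation and so have to be measured and adjusted for in analysis where possible". Under Trial design, both waves come from the same people: "two cohorts have been established and will be followed up over 24 months in each of the intervention and control factories", and "All the workers and management staff from these cohorts were interviewed at baseline, and will be interviewed in the endline".

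**The concern.** Each factory joined on the basis of its own preference for one arm, and there are only four per arm. The comparison is therefore only as good as its covariate adjustment. A test of baseline difference measures imbalance and sample size. It does not show whether a variable affects the outcome, which is the other half of confounding. A strong predictor with a moderate, non-significant imbalance can be left out. A harmless variable can be brought in because the test ignores that workers are grouped in eight factories.

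The between-wave tests have a separate fault. The endline sample is what remains of the baseline sample, so the two are not independent. If the comparison is meant to show whether loss to follow-up has changed the cohort, a test for independent samples is the wrong instrument. The article itself expects job mobility, and the arms differ sharply on a likely driver of it: "54% of workers had been working there for less than 2 years, compared to 20% of those in the control factories".

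**Working it through.** **1. What kind of test is in use.** Management education in Table 3 can be rebuilt from its percentages. They fit 195 intervention and 199 control staff (one control value apparently missing):

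| Years of education | Intervention | Control |
|---|---|---|
| 1-5 | 7 | 14 |
| 6-10 | 95 | 107 |
| 11-12 | 60 | 42 |
| 13-15 | 19 | 25 |
| over 15 | 14 | 11 |

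The ordinary Pearson chi-square, Σ(O − E)²/E, gives 7.36 on 4 df, p = 0.118, exactly as printed. The published baseline comparison is thus reproduced by a test that treats staff as independent of their factory.

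**2. What the rule selects.** The same test on worker counts rebuilt from Table 3 (rounding leaves row totals within 3 of 400) gives:
- age: 65.8 on 4 df;
- education: 33.9 on 5 df;
- duration of work: 105.3 on 2 df.

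All have p < 0.00001, so all three enter. Management education, at p = 0.118, does not, although the 11-12 year group differs by 30.8 − 21.1 = 9.7 percentage points. For a binary worker characteristic at 50%, with 400 per arm, any gap below 1.96 × √(0.25 × 2/400) = 6.9 points is non-significant.

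**3. How the test behaves with eight factories.** The article gives no intracluster correlation (ICC), so a range is assumed. With 100 workers per factory the design effect is 1 + 99 × ICC. With no true arm difference, a nominal 5% test rejects with probability of about 2 × [1 − Φ(1.96/√DE)]. Simulation (20,000 runs) gave:

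| Assumed ICC | Design effect | Rejection rate |
|---|---|---|
| 0 | 1.00 | 5% |
| 0.01 | 1.99 | 16% |
| 0.02 | 2.98 | 26% |
| 0.05 | 5.95 | 43% |
| 0.10 | 10.9 | 56% |

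**4. The between-wave test.** Assumptions: a fixed trait held by 50% of 800 workers, and 20% lost overall (the article's allowance), split 25% among those with the trait and 15% among those without. Factory clustering is ignored in this step.
- Retained: 300 of 640 have the trait, 46.9%. Lost: 100 of 160, 62.5%.
- Baseline v endline as independent samples: difference 50.0 − 46.9 = 3.1 points; pooled proportion 700/1,440 = 0.486; SE = √[0.486 × 0.514 × (1/800 + 1/640)] = 0.0265; expected z = 1.18.
- Lost v retained: difference 15.6 points; SE = √[0.25 × (1/640 + 1/160)] = 0.0442; expected z = 3.54.

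The wave difference is 160/800 = 0.2 times the lost-retained difference, so its real SE is about 0.2 × 0.0442 = 0.0088. The independent-samples formula uses a value three times too large. Detection rates in simulation, with the same loss pattern in both arms:

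| Loss by trait | Wave test, 800 | Lost v retained, 800 | Wave test, one arm of 400 | Lost v retained, one arm of 400 |
|---|---|---|---|---|
| 20% v 20% | 0% | 5% | 0% | 5% |
| 25% v 15% | 1% | 94% | under 0.1% | 71% |
| 30% v 10% | 88% | 100% | 19% | over 99% |

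If the 30/10 pattern runs in opposite directions in the two arms, the pooled wave test detects it in 0% of runs and the within-arm wave test in 20%. Lost v retained within an arm detects it in over 99%.

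**The case against.** Several stronger readings are tempting, and the article does not support them.

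- A reader might infer that covariates enter only if a test is significant. That is not what the section says: adjustment for baseline rates and for factors associated with the outcomes has no test condition, and Limitations commits to adjusting for measured confounders. This stands. What remains is that two rules are given, neither lists variables, and their relation is not stated.
- A reader might infer that endline tenure or earnings, which the intervention could alter, will be adjusted for. The sentence speaks of pre-existing differences, which points to baseline values.
- A reader might infer that differential dropout will go unseen. The article never calls the wave comparison an attrition check. Cohort tracking includes contact every two months and recording of reasons for dropout. The endline test between arms would pick up a strong pattern in opposite directions (89% of simulated runs), though only 35% if the 30/10 pattern occurs in the intervention arm alone.
- A reader might argue that a clustered test would drop worker education. That is a test the protocol does not use. Ignoring factories makes the tests too liberal, so it lets covariates in.

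It can also be said that covariate lists and missing-data methods belong in an analysis plan that is not shown. That is fair for what is absent. The point here concerns a procedure that the article does state.

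**Conclusion.** The point holds in a limited form. The stated rule makes part of the confounder control depend on significance tests, in a non-randomised comparison of four with four factories, and names no allowance for factories. Its one visible consequence in Table 3 is management education, which the rule would not select at p = 0.118, although the sentence on factors associated with the outcomes could still bring it in. Worker age, education and tenure are selected as things stand.

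Applied between waves, the tests break independence whatever their purpose. As a screen for selective loss they are nearly blind to a moderate pattern: about 1% against 94%. That contrast rests on an assumed 50% trait, 25% v 15% loss, comparison of a fixed trait and no clustering. The rejection rates in step 3 rest on assumed ICCs. No bias in the eventual effect estimate has been demonstrated. This should be changed, but it does not invalidate the trial.

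**What to change.** Remove the significance condition. State one covariate set, at baseline values, for all analyses: the respondent's own baseline outcome, age, education and tenure in the factory, with earnings added for managers. Whether worker earnings belong in the set should be settled on subject-matter grounds, not by their p = 0.290. State that this set is what the sentence on factors associated with the outcomes refers to.

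Replace the baseline-versus-endline tests with a table, within each arm, of baseline characteristics of those interviewed at endline and those lost, read by the size of the differences. Inverse-probability weighting or multiple imputation on the same variables can serve as a sensitivity analysis.

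The covariates named are in Table 3, and the baseline outcomes come from the baseline interviews. The cost is revised wording, a few individual-level covariates and a little analysis work.

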### Sample size

For the worker survey, the sample size calculation was based on the primary outcome – physical IPV against female garment workers. Expecting 56% baseline prevalence of past year physical IPV experienced by the female garment workers (icddr,b unpublished data), and anticipating a 20% effect size, 5% level of significance and 80% power, the required sample size was 330 workers for both the intervention and control groups. To account for a 20% lost to follow up the sample size increased to 396 workers for both the groups, which was rounded up to 400. Thus, a sample of 100 workers would be required from each of the intervention and control factories, giving 800 in total.

For the management survey, the sample size calculation was based on gender inequitable attitudes among garment management staff. Anticipating 50% baseline prevalence of high or moderate gender equitable attitudes among the management staff, a 30% effect size, 5% level of significance and 80% power, the required sample size was 183 management staff for both intervention and control groups. Anticipating 10% loss to follow up, the sample size increased to 200 for both the groups. Thus a sample of 50 management staff would be required from each of the intervention and control factories, giving 400 in total.

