### Recruitment and allocation

BSR works with a network of international brands and buyers via HERproject, a women empowerment initiative in the supply chain, in Bangladesh, and both intervention and control factories in HERrespect were recruited through buyers as per the selection criteria, through one-on-one engagement and a suppliers’ workshop. Four buyers participated in nominating eight factories (four intervention and four control) to join HERrespect. Participant factories had strict preference for being included as an intervention factory or control factory and were recruited on that basis. Care was taken to select control factories at a distance from the intervention factories to prevent potential contamination. Also, preference was given to factories that had not recently completed similar training programs or interventions in gender-based violence.

Each factory provided a self-selected list of 315 workers from their full list of workers. A listing was then carried out of these selected 315 workers within each factory mainly for the purpose of screening eligibility. Once eligibility had been established and agreement to participate given, 100 workers were randomly selected from each factory. The workers from the intervention factories were then assigned to group sessions and interviewed at baseline. If more than one worker belonged to the same household, one was chosen randomly for participating in the study. Each factory provided a self-selected list of 50 management staff having direct interaction with workers. This cohort of management staff are interviewed at baseline and endline. However, all management staff received the group sessions.

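### Arm was set by factory (four against four), but the stated analysis and sample size make no allowance for factory clustering, so outcome standard errors will be too small if workers within a factory are at all alike

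*Protocol article*

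**What the plan says.** On the design, the Trial design section says of the trial: "It is being conducted in four intervention and four control factories". Recruitment and allocation explains how factories reached an arm: "Participant factories had strict preference for being included as an intervention factory or control factory and were recruited on that basis". Within each factory 100 female workers form the cohort. Several components (sessions for all middle managers, policy review, factory-wide campaigns) act on the factory as a whole.

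On the analysis, Statistical methods: Data analysis says the impact on the main outcomes "will be assessed using risk ratios derived from binary regression analyses adjusting for baseline rates", with further adjustment for factors associated with the outcome and the same approach for secondary outcomes. Before that, "Chi-square (for categorical variables) and t-tests (for continuous variables) will be performed" to compare background characteristics between arms and between survey rounds. Differences found this way are then controlled for. Neither this section nor any other mentions clustering, an ICC, a design effect, a factory effect or a clustered variance. The Limitations section discusses non-random allocation, location and attrition, but not clustering.

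On the sample size, the worker calculation starts from "Expecting 56% baseline prevalence of past year physical IPV experienced by the female garment workers" and continues: "anticipating a 20% effect size, 5% level of significance and 80% power, the required sample size was 330 workers". The attrition step reads: "To account for a 20% lost to follow up the sample size increased to 396 workers for both the groups". The result is rounded to 400 per arm and divided by four factories.

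**The concern.** When the arm is a property of the factory, the evidence on the arm effect comes from eight units. Women in one factory share managers, policies and district, so their answers are likely to be correlated to some degree. A model that treats each woman as an independent observation counts that shared variation as extra information, and its standard errors and confidence intervals come out too small. An ordinary difference between two sets of four factories could then be reported as an intervention effect and used to support scale-up.

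The mechanism is clearest for the workplace-violence primary outcome. It counts acts a woman saw as well as acts done to her, so one manager's conduct can be reported by many sampled women. It is weaker, though not absent, for the three primary outcomes on violence by a husband.

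**Working it through.** **1. Was independence assumed? Reproduce the stated sample size.** Inputs from the Sample size section: 56% prevalence, a 20% effect read as relative (0.56 × 0.8 = 0.448), 5% significance, 80% power. Sidedness is not stated; two-sided is inferred because it gives the stated figure.

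- Pooled proportion: (0.56 + 0.448)/2 = 0.504; difference d = 0.112.
- n = [1.96·√(2·0.504·0.496) + 0.842·√(0.56·0.44 + 0.448·0.552)]² / 0.112² = (1.386 + 0.591)²/0.01254 = 311.7, so 312 per arm.
- With continuity correction: n' = (n/4)·[1 + √(1 + 4/(n·d))]² = 329.3, so **330 per arm**, the stated figure.
- Attrition step: 330 × 1.2 = 396, rounded to 400, then 400/4 = 100 per factory.

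The management figure behaves the same way. 50% against 35% (or 65%) gives 170 without and **183** with continuity correction, and 183 is the stated number. Both calculations therefore use a design effect of 1.

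**2. A second trace of the same assumption.** Table 3 prints P = 0.118 for management education. Counts rebuilt from its percentages are 7/95/60/19/14 of 195 (intervention) and 14/107/42/25/11 of 199 (control). An ordinary Pearson chi-square on these gives 7.36 on 4 df, p = 0.118. The baseline comparison was made without regard to factory.

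**3. Type I error of a nominal 5% test.** Design effect DE = 1 + (m − 1)·ICC; true type I error = 2·[1 − Φ(1.96/√DE)]. Here m is the number analysed per factory: 80 after the planned 20% loss, or 100 with no loss. The ICC is not in the document, so the range is an assumption.

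| ICC | DE (m = 80) | SE too small by factor √DE | Type I error, m = 80 | Type I error, m = 100 |
|---|---|---|---|---|
| 0.001 | 1.08 | 1.04 | 5.9% | 6.2% |
| 0.005 | 1.40 | 1.18 | 9.7% | 10.9% |
| 0.01 | 1.79 | 1.34 | 14.3% | 16.5% |
| 0.02 | 2.58 | 1.61 | 22.2% | 25.6% |
| 0.05 | 4.95 | 2.22 | 37.8% | 42.2% |

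A beta-binomial simulation (four against four factories, 40,000 runs per setting, true rate 50%) agrees. The unclustered test rejected in 14.9% to 38.9% of runs for m = 80 and 16.9% to 42.5% for m = 100, over ICC 0.01 to 0.05. A t-test on the eight factory proportions (6 df) stayed at about 5% throughout. Both the formula and the simulation describe an unadjusted endline comparison.

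**4. Power when the factory is the unit.** For 56% against 44.8% with m = 80: effective n per arm = 320/DE; SE = √[(0.56·0.44 + 0.448·0.552)/effective n]; noncentrality = 0.112/SE; critical value t(0.975, 6 df) = 2.447.

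| ICC | Effective n per arm | SE | Noncentrality | Power |
|---|---|---|---|---|
| 0.01 | 179 | 0.0526 | 2.13 | 43% |
| 0.02 | 124 | 0.0631 | 1.78 | 32% |
| 0.05 | 65 | 0.0874 | 1.28 | 19% |

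**The case against.** The strongest reply is that this is an argument from silence. The analysis section is one paragraph of a journal article and the analysis plan is not shown. Binary regression can carry a factory random effect or be fitted by GEE, and a condensed article need not say how standard errors are computed. That would be a fair answer if the article were merely silent, but both sample sizes reproduce only with a design effect of 1, and a printed baseline P-value is an unclustered chi-square. An unseen plan could add a factory term, but it could not make the published sample size allow for clustering.

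Other parts of the reply stand:

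- **No unconditional error rate.** A reader might infer that the planned tests will have a false-positive rate of 15% to 38%. The documents do not support that, because no ICC is given. At ICC 0.001 the inflation is about one percentage point. The figures also depend on how many women per factory are analysed, and baseline and covariate adjustment may lower the residual correlation.
- **The chi-square and t-tests are not outcome tests.** A reader might count them as part of the outcome analysis. The article confines them to background characteristics. Their fault is narrower: being unclustered, they will flag too many differences and so steer the choice of covariates.
- **Clustering is not confounding.** A reader might infer that a factory-level analysis would make the comparison sound. Factories chose their arm, and no variance correction addresses that.

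**Conclusion.** The point holds. Arm was assigned by factory, the stated analysis makes no allowance for it, and the sample size shows that workers were treated as independent. The direction is certain for any positive residual within-factory correlation: outcome standard errors too small, intervals too narrow, tests too liberal.

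The size is conditional. For an unadjusted comparison with about 80 women per factory, true type I error runs from about 6% (ICC 0.001) through 10% (0.005) to 14%, 22% and 38% (0.01, 0.02, 0.05). With all 100 per factory it is about 17% to 42% over ICC 0.01 to 0.05. Confidence is high in the missing allowance and lower in any single figure. This should be corrected before the endline data are analysed.

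**What to change.** Make the factory the unit of inference for all worker and management outcomes, by one of two routes:

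- baseline- and covariate-adjusted factory summaries, compared between arms on 6 degrees of freedom and expressed as a risk ratio or mean difference; or
- a mixed model or GEE grouped by factory, with a small-sample correction. Uncorrected sandwich standard errors should not be used with eight clusters.

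Choose the adjustment covariates on substantive grounds, not by unclustered significance tests. A permutation test over the 70 possible four-against-four splits (smallest two-sided p = 2/70 = 0.029) may be reported only as a sensitivity check. It must assume that factories are exchangeable, because arms were not randomised.

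Restate the 80% power with an explicit ICC assumption and range, using the figures in step 4 of the working.

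The change needs no new data, only revised analysis wording and some programming. The real cost is wider intervals and a stated power well below 80%. Confounding from factories choosing their arm must still be handled and reported separately.
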